### Primary Endpoint

The primary endpoint is 5-year clinical relapse-free survival (cRFS), defined as the absence of any cR that would be visible at top of the line imaging (see below). Any detected clinical recurrences (r) would be anatomically mapped and categorized as local (rL), pelvic nodal (rN1), retroperitoneal nodal (rM1a), bone (axial, perpendicular, or both, rM1b), or soft-tissue (rM1c). Combinations of different relapse sites are of course possible and will be reported accordingly. Apart from the anatomical site of relapse, the number of relapses, size per relapse, and the subsequent treatment will be recorded.

PSA measurements are performed during follow-up according to a fixed schedule (Table 1). If PSA is undetectable, patients are considered free of cR. In case of biochemical relapse, defined as PSA >0.2 µg/L in the postprostatectomy setting and PSA >nadir+2 µg/L in the primary setting [39,40]. In addition, positron emission tomography-CT (PET-CT) imaging using prostate-specific membrane antigen ligand or ^18^F/^11^C-choline- based PET-CT imaging is acquired. Additional imaging tools include multiparametric MRI and MRI of the axial and perpendicular bones. The decision to perform additional imaging will be taken after multidisciplinary consensus in all cases.

**Table 1 table1:** Standard Protocol Items: Recommendations for Interventional Trials 2013 diagram: Para-Aortic Radiotherapy (PART)-trial.

Timepoint		Study period					
		Enrollment: Screen visit & pre-PART (-t_1_)	Postallocation				
			During PART		Follow-up		
			Weekly	Last day	Month 1, 3, 6, 9, 12	Month 18, 24, 30, 36, 42, 48, 54, 60	Year 6 up to year 10, yearly

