### Secondary Endpoints

Secondary endpoints are quality of life (QoL), treatment-related acute and late toxicity, time to palliative ADT, time to castration-refractory prostate cancer (CRPC), CSS, and in-field pelvic and para-aortic disease control.

The QoL is measured using the European Organization for Research and Treatment of Cancer (EORTC) core questionnaire [41]. In addition, the EORTC prostate cancer module [42], the EuroQol 5 dimensions questionnaire [43], the International Consultation on Incontinence Short Form score [44], and the International Index of Erectile Function scoring system [45] are used to assess urinary, bowel, and sexual functioning and symptoms and evaluate the side effects of hormonal treatment associated with radiotherapy. QoL questionnaires are handed over to patients before treatment (baseline score) and at well-defined time points (end of treatment; 1 month, 3 months, 6 months, and 9 months after treatment; every 6 months until 5 years after treatment; and every 12 months until 10 years after treatment). QoL results will be presented in accordance with guidelines for reporting health-related QoL outcomes in cancer clinical trials published by the EORTC [46].

Treatment-related toxicity is assessed using the Common Toxicity Criteria for adverse events version 4.0 (CTCAE v4.0) [47]. Abdominal pain, diarrhea, enterocolitis, fecal incontinence, flatulence, hemorrhoids, proctitis, rectal fistula, rectal hemorrhage, rectal pain, noninfectious cystitis, hematuria, urinary frequency, urinary incontinence, urinary retention, urinary tract pain, erectile dysfunction, and fatigue are scored as adverse events according to CTCAE v4.0. Symptoms are scored before treatment. In addition, PART-induced acute toxicity (CTCAE v4.0) is scored weekly during radiation treatment and 1 month and 3 months after treatment. Furthermore, treatment-induced late toxicity (CTCAE v4.0) is scored at 6, 9, and 12 months after treatment; every 6 months until 5 years after treatment; and every 12 months until 10 years after treatment.

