Time to palliative ADT is defined as the secondary endpoint of this trial. Indications to initiate palliative ADT are based on the EAU guidelines [39,40] and include the following: PSA>50 µg/L or PSA doubling time <6 months or symptoms due to progressive disease. In case of oligometastatic recurrence (1-3 synchronous metastases), metastasis-directed therapy is the preferential treatment option [48]. Time to CRPC is defined according to the criteria defined in the EAU guidelines [39,40]. CSS is defined as the interval from the date of diagnosis to the date of death from PCa or to the last follow-up date for censoring purposes, if the patient is alive and is still being followed at the time of data cut-off.

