### Time Schedule

The aim is to recruit the necessary number of patients within a timeframe of 48 months. Follow-up of these patients will be lifelong to correctly estimate the primary and secondary endpoints. Reports on acute PART-induced toxicity and QoL will be expected within 6 months of the closure of the trial. Furthermore, the primary endpoint will be calculated after a median follow-up of 60 months.

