### Sample Size and Statistics

We aim to improve 5-year cRFS by 15% (primary endpoint). This would result in a 5-year cRFS of 75% compared with the control group with WPRT only that reaches a 5-year cRFS of 60% [18,20]. For a log-rank test comparing two survival curves with a one-sided significance level of .1, assuming uniform accrual with an accrual time of 48 months and a follow-up time of 12 months, a sample size of 137 is required to obtain a power of at least 80%. Taking into account a dropout of 10%, we aim to include 151 patients. The control group consists of pN1 patients treated with adjuvant ADT and WPRT alone from whom the data have been published before [20]. The incidence of acute and late toxicity will be recorded. In addition, actuarial risk estimates for developing acute and late toxicity will be calculated using Kaplan-Meier analysis. Time to palliative ADT, time to CRPC, CSS, and in-field pelvic and para-aortic disease control will be calculated using Kaplan-Meier actuarial analysis. cRFS, time to CRPC, CSS, and in-field pelvic and para-aortic disease control times are defined from the date of LN dissection until an event or last follow-up. Statistical analysis will be performed using the latest version of SPSS (IBM Corp, Armonk, NY, USA).

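### Kaplan-Meier is fixed for late toxicity, palliative ADT, CRPC, cause-specific survival and in-field control, so deaths without the event are censored and each absolute risk is modestly overstated, mainly at 10 years

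*Protocol article*

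**What the plan says.** The estimator is fixed in Sample Size and Statistics. After stating that toxicity incidence will be recorded, the section adds that "actuarial risk estimates for developing acute and late toxicity will be calculated using Kaplan-Meier analysis". It continues: "Time to palliative ADT, time to CRPC, CSS, and in-field pelvic and para-aortic disease control will be calculated using Kaplan-Meier actuarial analysis". No competing-risk method appears anywhere in the article.

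The same section gives the time rule for cRFS, CRPC, cause-specific survival and in-field control: "in-field pelvic and para-aortic disease control times are defined from the date of LN dissection until an event or last follow-up". That leaves two outcomes, event or last follow-up. Toxicity and time to palliative ADT are not in that list. For cause-specific survival, Secondary Endpoints runs the interval to the "date of death from PCa or to the last follow-up date for censoring purposes", and censoring is described for patients who are still alive. Death from another cause is not mentioned.

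The horizons are long. Time Schedule says: "Follow-up of these patients will be lifelong to correctly estimate the primary and secondary endpoints". Under Secondary Endpoints, late toxicity is scored at intervals that end with "every 12 months until 10 years after treatment". Acute toxicity is "scored weekly during radiation treatment and 1 month and 3 months after treatment".

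**The concern.** Kaplan-Meier knows only two states, event and censored. A man who dies before late toxicity, CRPC, palliative ADT or in-field failure has had none of these events, so the estimator must treat him as censored. It then in effect counts him as still able to have the event later. The same holds for a man who dies of another cause in the cause-specific survival analysis. One minus Kaplan-Meier then describes a world without other deaths, and it exceeds the proportion of patients who actually experience the event.

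The article calls the toxicity quantity a risk, and its Discussion wants the trial to support the design of a later phase III study. Absolute rates of late toxicity and in-field failure are natural inputs to such a design. The gap widens with follow-up, and the article says late toxicity and the other secondary time-to-event results will be published after longer follow-up.

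**Working it through.** **Plan's own figures.** The article states no expected rate for any of these endpoints, so there is nothing to reproduce. Its one calculated figure, the sample size of 137 for the log-rank comparison of cRFS, does not enter this point.

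**Direction.** Both estimators sum the same hazard increments (events divided by number at risk). Kaplan-Meier weights each increment by survival free of the event alone, and Aalen-Johansen weights it by survival free of the event and of death. The second weight is never the larger, so one minus Kaplan-Meier is never below the cumulative incidence. This needs no outside data.

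**Inputs for size.** The Introduction gives 5-year prostate cancer-specific survival above 90%, that is, prostate-cancer mortality below 10%. Other-cause mortality is not given. Assumptions: 3-10% competing deaths by 5 years, constant hazards, and illustrative Kaplan-Meier risks of 10%, 20% and 40% at 5 years.

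**Formulas.** With event hazard λ and competing hazard μ per year:
- one minus Kaplan-Meier at t: 1 − exp(−λt)
- cumulative incidence at t: λ/(λ+μ) × [1 − exp(−(λ+μ)t)]

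**Worked case, 20% at 5 years.** λ = −ln(0.80)/5 = 0.0446.
- 3% deaths: μ = −ln(0.97)/5 = 0.0061 and λ/(λ+μ) = 0.880. At 5 years, 0.880 × (1 − 0.80×0.97) = 0.197. At 10 years, 0.880 × (1 − 0.776²) = 0.350.
- 10% deaths: μ = −ln(0.90)/5 = 0.0211 and λ/(λ+μ) = 0.679. At 5 years, 0.679 × (1 − 0.80×0.90) = 0.190. At 10 years, 0.679 × (1 − 0.72²) = 0.327.

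One minus Kaplan-Meier at 10 years is 1 − 0.80² = 36.0%.

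| 1−KM at 5 y | Cumulative incidence at 5 y | Excess (points) | 1−KM at 10 y | Cumulative incidence at 10 y | Excess (points) |
|---|---|---|---|---|---|
| 10% | 9.9-9.5% | 0.15-0.5 | 19.0% | 18.5-17.2% | 0.6-1.8 |
| 20% | 19.7-19.0% | 0.3-1.0 | 36.0% | 35.0-32.7% | 1.0-3.3 |
| 40% | 39.5-38.1% | 0.6-1.9 | 64.0% | 62.4-58.7% | 1.6-5.3 |

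Each range runs from 3% to 10% competing deaths by 5 years.

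**Acute toxicity.** With an assumed 30% risk at 3 months and 0.1-1% deaths per year, the excess is below 0.04 points.

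**The case against.** The strongest defence is that the effect is small and confined to secondary endpoints. At 5 years it is about a point or less for a 20% risk. Toxicity is not reported on the Kaplan-Meier scale alone, because the recorded incidence comes first and the actuarial estimate is an addition. The only comparison specified with the historical group is cRFS, and no decision rule rests on these estimates. Kaplan-Meier also matches how earlier series were published. All of this stands, and it limits the weight of the point. It does not remove it: a crude incidence does not handle incomplete follow-up, and the estimator for these endpoints is fixed in the text.

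The article does not say in words that deaths are censored. That follows from the estimator and the event definitions. For toxicity and palliative ADT it follows from the estimator alone, since the stated time rule does not name them.

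A reader might infer three stronger things that the article does not support:

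- **Relapse as the competing event.** Competing rates of 20-40%, in the range of the planned relapse rates, would turn a Kaplan-Meier risk of 20% into 18.0-15.8%, an excess of 2.0-4.2 points. But relapse does not preclude toxicity, CRPC or palliative ADT. Toxicity scoring has no stop at relapse, and progressive disease is itself an indication for palliative ADT. The 40% is also the control group's figure; the PART group is planned at 25% relapse of all kinds.
- **Out-of-field relapse as precluding in-field failure.** Primary Endpoint expects combinations of relapse sites, and nothing says that out-of-field relapse is censored. Even if it were, a split that fits 75% cRFS, such as 10% in-field and 16.7% out-of-field (1 − 0.90×0.833 = 0.25), gives 9.2% against 10%, an excess of 0.8 points. Making it a competing event would change the question from control of the irradiated volume to site of first failure.
- **A biased primary analysis.** cRFS is "defined as the absence of any cR that would be visible at top of the line imaging", and the handling of death is not stated there. If deaths are censored, the log-rank test still compares relapse hazards. If deaths count as events, there is no competing risk.

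**Conclusion.** The point holds for late toxicity, time to palliative ADT, time to CRPC, cause-specific survival read as a risk of prostate-cancer death, and in-field control. The direction is certain once deaths without the event are censored, which the chosen estimator forces.

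The size rests on assumed competing mortality of 3-10% by 5 years and constant hazards: about 0.3-1.0 points on a 20% risk at 5 years, and about 1.0-3.3 points on the matching 36% at 10 years. If mortality rises with age, the 10-year excess would be larger than shown. The point matters mainly for late toxicity and other results reported out to 10 years. It is negligible for acute toxicity and does not touch the primary log-rank test or the sample size. It is a worthwhile correction of modest size.

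**What to change.** In Sample Size and Statistics, name the Aalen-Johansen cumulative incidence as the main estimate for late toxicity, palliative ADT, CRPC, prostate-cancer death and in-field failure. Use death as the competing event, and death from other causes where the event is prostate-cancer death. Keep Kaplan-Meier as a supportive figure for comparison with published series.

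For in-field failure, do not make out-of-field relapse a competing event in the main analysis; continue to count in-field failures that occur after it. A cumulative incidence by site of first failure can be shown, at most, as a supplementary description.

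No new data should be needed, since the article already provides for reporting deaths and mapping relapse sites. The cost is one paragraph of wording and a few lines of code, possibly in software other than SPSS. The small downside is that the main figures compare less directly with published Kaplan-Meier rates, which the supportive figure covers.

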## Results

Ethical approval to conduct this study (version 2.0 from December 1, 2016) was granted by the Medical Ethics Committee University Hospitals/Catholic University Leuven (14/12/2016). Written informed consent of patients is mandatory before recruitment. Recruitment of patients started in 2017 and is expected to be completed by March 2020.

As a result of the PART trial, we will publish the 5-year cRFS, defined as the absence of any cR that would be visible at top of the line imaging, our primary endpoint. Furthermore, we will compare these results with the 5-year cRFS of a historical control group of patients who underwent WPRT; the results of this historical control group have already been published by Poelaert et al [20]. This control group includes patients with PCa who underwent PLND and pelvic radiotherapy between January 2000 and January 2016 at a tertiary center (GUH). Those patients were rigorously treated by several authors of this manuscript ([name], VF, [name], and NL). A total of 154 pN1 patients with PCa who received WPRT were included. As described in the “Sample size and Statistics” section, survival curves of both groups will be compared using log-rank test. Besides, acute toxicity and QoL results will be published after short-term follow-up, whereas treatment-related late toxicity and QoL results, time to palliative ADT, time to CRPC, CSS, and in-field pelvic and para-aortic disease control will be published after a longer follow-up period.

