## Introduction

Prostate cancer (PCa) is the most common nonskin malignancy and an important cause of cancer-related mortality in men in industrialized countries worldwide [1,2]. Mortality is highest in patients with high-risk PCa, defined by the guidelines of the European Association of Urology (EAU) as T-stage ≥cT2c or Gleason score ≥8 or prostate-specific antigen (PSA) >20 ng/mL. These patients benefit from aggressive local treatment (surgery with or without adjuvant radiotherapy or primary radiotherapy). To assess the risk of disease spread to pelvic nodes, predictive nomograms are used [3-5], although the EAU guidelines consider an extended pelvic lymph node dissection (ePLND) as a necessity in high-risk patients [6]. Indeed, ePLND has proven to be the most accurate nodal staging procedure and, therefore, remains the gold standard [7] with even a positive effect on PCa mortality, certainly in case of limited nodal disease [8] and negative nodes [9].

Historically, patients with positive pelvic lymph nodes (LNs; N1) were considered metastatic and treated with lifelong palliative androgen deprivation therapy (ADT) only [10]. However, in the 21st century, an important paradigm shift occurred. First, local treatment with curative intent is gaining interest in patients with N1 disease [11]. Hereby, also the extent of ePLND plays a crucial role in predicting cause-specific survival (CSS) as demonstrated by Abdollah et al [12]. Second, large retrospective series demonstrated an improvement in prostate cancer-specific survival (PCSS) when postoperative radiotherapy was added to ADT in pathologically node-positive (pN1) patients [13-15].

In the multidisciplinary approach for pN1 patients, multimodality treatment consisting of treatment of the primary tumor, long-term ADT, and whole pelvic radiotherapy (WPRT) has become the standard of care at the Leuven University Hospitals (LUH; Leuven, Belgium) and at the Ghent University Hospital (GUH; Ghent, Belgium). WPRT is delivered using intensity-modulated or volumetric modulated arc therapy (IMAT/VMAT) [16,17]. Clinical results demonstrated that this multimodality treatment is well tolerated and results in 5-year PCSS of >90%, with the best results observed in patients having a low number of positive LNs. Indeed, patients presenting with 1 or 2 positive LNs had a 5-year PCSS comparable to that of pN0 patients [18-20].

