The number of pathologically metastatic LNs is a determinant for patient outcome. In case >2 LNs are pathologically invaded by the tumor, 30%-40% of the patients relapse biochemically and clinically [21,22]. Furthermore, some data suggest that extracapsular extension of pelvic nodal metastases is an important negative prognostic factor in pN1 patients [23].

Reportedly, clinical relapse (cR) is present in the para-aortic LNs (PALN, M1a disease) in up to 77% of the cases [24,25]. Rischke et al demonstrated the retroperitoneum to be the most frequent site of relapse after pelvic salvage treatment [26]. In the TNM classification, patients with positive PALN are denominated M1a disease and considered as a separate entity [27]. We hypothesize that these positive PALNs will lead to further hematogenous spread (M1b-M1c disease [27]) and that elective para-aortic irradiation will decrease the rate of further metastatic spread, postpone the need for palliative ADT, and prolong the time to castration-refractory disease. To test this hypothesis, we designed a prospective, nonrandomized phase II trial to evaluate the efficacy of elective para-aortic radiotherapy (PART) in pN1 patients compared with those who were historically treated with adjuvant WPRT alone (Figure 1).

This trial is novel and unique as it is the first to investigate the irradiation of the PALN region in pN1 patients with PCa to prevent further metastasis. This strategy has already been evaluated in advanced cervical cancer, but to the best of our knowledge, never in patients with PCa.

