### Inclusion and Exclusion Criteria

Men aged >18 years with histologically proven adenocarcinoma of the prostate at biopsy (cT1-4) who are referred for primary high-dose radiotherapy or patients after radical prostatectomy (RP; pT2-4) with presence of pN1 disease after ePLND are eligible for the study. pN1 disease is defined as the presence of regional LN metastasis in the true pelvis. These regions include the common iliac nodes, presacral nodes, external and internal iliac nodes, and obturator nodes [27]. In all participating centers, performing an ePLND is the standard of care in high- intermediate and high-risk patients, independent of whether the primary treatment is RP or high-dose radiotherapy [7,28]. If pN1 disease is present, patients are eligible if one of the following criteria is fulfilled:

Two or more positive LNsPositive LNs/removed LNs >7%Presence of extracapsular metastatic extension at the level of any LN

ePLND is defined as the removal of LNs around the external and internal iliac vessels and in the obturator fossa. Removal of additional LNs in the presacral area or around the common iliac vessels is at the discretion of the treating physician (but strongly advised if present on preoperative imaging). The minimum harvest of removed LNs that is considered representative is set at 14. Textbox 1 summarizes the inclusion and exclusion criteria.

After amending, patients with pN1 disease in the salvage setting will be allowed in the PART trial and will be prospectively followed with the same treatment protocol and study design to obtain data about acute and late toxicity. These data will be analyzed separately and will not interfere with the initial set-up of statistics.

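### The primary log-rank test compares nodally selected PART patients with 154 historical pN1 controls not described as meeting the same criteria, without adjustment, so case-mix is mixed with treatment effect

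*Protocol article*

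**What the plan says.** *Inclusion and Exclusion Criteria* (protocol article) limits entry among men with pN1 disease: "patients are eligible if one of the following criteria is fulfilled". The criteria are two or more positive nodes, a positive-to-removed ratio above 7%, or extracapsular extension at any node. On the dissection it adds: "The minimum harvest of removed LNs that is considered representative is set at 14".

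*Sample Size and Statistics* names the comparator: "The control group consists of pN1 patients treated with adjuvant ADT and WPRT alone". It sets the planning rates at 60% (control) and 75% (PART) and the test: "For a log-rank test comparing two survival curves with a one-sided significance level of .1". *Results* describes the same comparator: "A total of 154 pN1 patients with PCa who received WPRT were included". These men had PLND and pelvic radiotherapy at one tertiary centre (GUH) from January 2000 to January 2016. The section repeats that the two survival curves will be compared by log-rank test. Neither section applies the PART nodal criteria or the harvest minimum to the controls, and neither mentions matching, stratification or covariates.

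On prognosis, the *Introduction* states: "The number of pathologically metastatic LNs is a determinant for patient outcome". It also cites extracapsular extension as an important adverse factor.

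**The concern.** The trial selects its patients on variables that its own rationale calls prognostic, then compares them with a group not described as selected in that way. The difference in 5-year cRFS then contains two things: the effect of adding para-aortic irradiation, and the difference in nodal burden between the cohorts. An unadjusted log-rank test cannot separate them.

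This historical contrast is the only comparison for the primary endpoint, and the article hopes that it will support a randomised phase III trial. If the controls include patients with a lighter nodal burden, a real benefit may be missed or understated. If differences in period, centre or staging favour the newer cohort, a benefit may appear that PART did not cause.

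**Working it through.** **1. The plan's own sample size.** Assume exponential cRFS, with λ = −ln(S)/60 per month. Then HR = ln .75 / ln .60 = 0.563.
- Event probability with uniform accrual A = 48 and further follow-up F = 12 months is 1 − [exp(−λF) − exp(−λ(A+F))]/(λA). This gives .259 for control and .157 for PART.
- Schoenfeld events at one-sided .10 and power .80: 4(1.282 + 0.842)² / (ln 0.563)² ≈ 55. Per group: 55/(.259 + .157) ≈ 132.
- Freedman's formula gives about 140 per group and Lachin-Foulkes about 138.

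The stated 137 is therefore reproduced as a per-group number. The sample-size arithmetic is not the problem.

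**2. Who the nodal filter removes.** One positive node out of 14 is 7.1% and qualifies; one out of 15 is 6.7% and does not. Given a harvest of at least 14, the excluded patients are those with a single positive node, 15 or more nodes removed and no extracapsular extension. The documents do not say what share of the 154 they make up.

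**3. Illustration of nodal case-mix.** Assumptions, not document figures: eligible controls have 60%; 30% of the 154 (46) are ineligible with 80%; 136 PART patients are analysed (151 × 0.9); cRFS is exponential; censoring is uniform from 36 to 84 months, a median of 60 as in *Time Schedule*. The log-rank test is simulated at one-sided .10.
- Pooled control: 0.7 × 60 + 0.3 × 80 = 66%. A true 15-point gain appears as 9 points.
- With no case-mix difference: power about .93, type I error about .10.
- With the mix: power about .66 (repeated simulations gave .65 to .67), type I error about .01.
- With ineligible shares of 20, 40 and 50%: power about .78, .52 and .37.

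**4. The same mix if 60% is the pooled rate.** Eligible controls are then at (60 − 0.3 × 80)/0.7 = 51.4%. Power for PART at 75% stays at about .93 to .94. The bias remains, because the visible gap is 15 points while the gap in comparable patients is 75 − 51.4 = 23.6.

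**5. The other direction.** Suppose PART has no effect, but period, centre or staging gives its patients a cRFS 5 points above a control at 60%. With 137 versus 154 patients and the 48+12-month event probabilities, the one-sided false-positive rate is about .29. At 10 points it is about .57. These offsets are also assumed.

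**The case against.** The strongest reply is that much of the mismatch is unproven. The make-up of the 154 lies in a cited publication that is not shown, the nodal filter is fairly mild (step 2), and covariate adjustment is often left to an analysis plan. The design is openly nonrandomised, and on nodal burden alone a positive result would be conservative.

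Part of this stands. The size of the bias cannot be computed, and several stronger readings that a reader might infer are not supported:
- *That the controls include PSA-recurrent patients.* The controls are described as adjuvantly treated, which argues against it.
- *That they were poorly dissected or poorly staged.* The article says PLND rather than ePLND and gives no harvest or imaging rule for them. That is silence, not evidence.
- *That the 60% planning rate is wrong.* It is the complement of the roughly 40% relapse that the *Abstract* gives for more than one positive node, and no fault in it is shown.
- *That power certainly drops to about .66.* This requires 60% to be the rate in eligible controls, whereas *Sample Size and Statistics* attributes it to the control group itself (step 4).
- *That the survival remark in the Introduction proves the cut-off separates prognosis.* The remark, "patients presenting with 1 or 2 positive LNs had a 5-year PCSS comparable to that of pN0 patients", concerns cancer-specific survival and groups PART-eligible two-node patients with single-node patients.

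The appeal to an unseen analysis plan does not dispose of the point. The article fixes both comparator and test, consistently, in two sections. It also keeps salvage patients out of the main statistics, so population differences were considered for one group and not for the controls.

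**Conclusion.** The point holds in a limited form. As written, the plan's only comparison for the primary endpoint sets a cohort selected on nodal burden against one not described as so selected, with no adjustment for factors that the protocol calls prognostic. Nodal selection by itself pulls the result against PART, lowering both the apparent benefit and the false-positive rate. Period, centre and staging may pull either way, so the net direction and size are unknown. It would go too far to say that no result could be informative: the defect is that the contrast cannot be attributed to PART without restriction and adjustment. All power and error figures in steps 3 to 5 rest on assumed control mixes or offsets and show a range, not an estimate.

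**What to change.** In *Sample Size and Statistics*, before outcomes are compared:
- Define the primary control group as those of the 154 who meet the PART nodal criteria, and the harvest of 14 where it is recorded.
- Prespecify a Cox or propensity-weighted comparison adjusted for baseline factors recorded in both cohorts: number of positive nodes, extracapsular extension, Gleason score, T stage, PSA and primary treatment (prostatectomy or radiotherapy). Leave out ADT duration: *Hormonal Treatment* fixes it at 24 months in PART, and it is determined after baseline.
- Keep the unadjusted log-rank test against all 154 as a sensitivity analysis.
- State the control cRFS in the restricted set and restate the power.

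The cost is fewer controls. If 30% are removed (108 left) or 50% (77 left), and the restricted rate is 60% against 75%, power is about .89 or .84 at a median follow-up of 60 months. Under the 48+12-month planning assumption it is about .76 or .71, below the 80% target. The fix also assumes that the treating centre can supply patient-level data; the article says that several authors treated these patients, but does not say that the data are available. Adjustment cannot remove differences of era, since the controls end in January 2016 and recruitment began in 2017. That limit should be stated with the result.
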